# A Multilingual, Culturally Competent Mobile Health Intervention to Improve Treatment Adherence Among Women Living With HIV: Protocol for a Randomized Controlled Trial

**DOI:** 10.2196/17656

**Published:** 2020-06-19

**Keywords:** telemedicine, HIV, acquired immunodeficiency syndrome, women, adherence, clinical trial protocol, barriers, facilitators, text messaging, mHealth, SMS/texting

## Abstract

**Background:**

Adherence to HIV care is complex, as barriers to care are multidimensional, particularly for ethnic minority women. Mobile health (mHealth) solutions are supportive in improving HIV health care outcomes. In the United States, however, mHealth interventions are not widely implemented in public HIV clinics and have not been customized for women. There is an unmet need for culturally and linguistically appropriate mHealth interventions that address the health care needs of minority women living with HIV.

**Objective:**

This study aims to describe a protocol investigating the feasibility of an mHealth intervention for treatment adherence among women living with HIV. This is a two-phase, mixed methods, pilot randomized controlled trial that begins with qualitative patient interviews to inform the system design. Participants will be block randomized by language (English, Spanish, and Haitian Creole) to 1 of 2 study arms.

**Methods:**

Women (age ≥18 years) who were followed up at the women’s HIV clinic of an academic medical center, with a recent history of nonadherence to HIV care (missed appointments, unsuppressed viral load, or not taking medications as prescribed), will be enrolled. The experimental arm will receive the intervention, which includes health reminders and psychoeducational messaging, plus clinical standard of care reminders. The psychoeducational messaging will target patient-level barriers of HIV stigma and medical mistrust and resilience as a patient-level strength. The control arm will receive standard of care reminders only (ie, mailed appointments and automated telephone calls). All aspects of the study and intervention will be offered in the participants’ preferred language. The primary outcome is the feasibility and acceptability of the study. The secondary outcomes are changes in self-reported medication adherence, depression symptoms, HIV stigma, medical mistrust, resilience, and clinic attendance and viral suppression extracted from the participants’ medical records. Data will be assessed at baseline (T0) and 2 subsequent clinic visits—approximately 3 to 4 months from the baseline (time 1; T1) and 6 to 9 months from the baseline (time 2; T2). Qualitative data will be transcribed and analyzed iteratively. Bivariate analyses will compare data by the study group (chi-square, odds ratios, and t tests). Exploratory analyses will be conducted for each outcome variable—T1 and T2 values will be compared with values at T0 by the study group.

**Results:**

As of March 2020, baseline quantitative data were collected on 54 participants (28 English speakers, 14 Spanish speakers, and 12 Haitian Creole speakers). The first 3 focus groups (1 in each of the 3 languages) were completed, with a total of 20 participants. The findings are currently being integrated into the beta version of the mHealth texting system.

**Conclusions:**

The findings of this novel HIV adherence intervention may shed light on the barriers and facilitators of HIV health care and the mechanisms of an mHealth intervention that is customized for ethnic minority women living with HIV.

**Trial Registration:**

ClinicalTrials.gov NCT03738410; https://clinicaltrials.gov/ct2/show/NCT03738410

**International Registered Report Identifier (IRRID):**

DERR1-10.2196/17656

## Introduction

### Background

Adherence to care (eg, visit adherence) is the single most important factor projected to improve health outcomes for persons living with HIV and reducing communal HIV viral load, relieving both the individual and public health burden of HIV [1]. Adherence to care is complex, as barriers are multidimensional. Barriers are experienced at the individual or patient level (ie, mental health and psychosocial) or can occur as a result of structural issues (ie, insurance coverage) [2]. In the United States, barriers to regular HIV care disproportionally affect women and ethnic minorities [3,4]. Metropolitan Miami has the highest HIV transmission rate in the United States; however, only 61% of women living with HIV are engaged in HIV care [5,6]. In Miami, a multicultural and multilingual region, two-thirds of the residents are foreign born and speak a language other than English. Specifically, 60% of the residents speak Spanish or Haitian Creole at home [7]. Mobile health (mHealth) technology, such as texting, has shown promise in improving HIV care adherence, both globally and domestically, in a variety of settings [8].

### Rationale

mHealth solutions, which range from texting to full-blown apps, are supportive in improving HIV health outcomes [8]; however, in the United States, where 95% of the residents own a mobile phone, mHealth is not widely implemented in public HIV clinics. Furthermore, most mHealth interventions in the United States for HIV care adherence are designed for specific populations such as sexual minority men or adolescents. Interventions tested among ethnic or linguistic minorities have focused on a single ethnic group and were monolingual. Furthermore, only a few have been designed for women [8]. Women access health care at specific life stages—pregnancy, primary, and gynecological care; these stages are opportunities to engage women in HIV care and address barriers to regular care. Among women, the frequency of engaging in care depends on their life stage. Postnatal women, who may be adequately engaged in HIV care, for example, fall out of care after the birth of their child [9]. Effective solutions need to reach all sectors of the population. Taken together, there is an unmet need for culturally and linguistically appropriate mHealth interventions that address the health care needs of women living with HIV.

Individual barriers to HIV care adherence are often interrelated and affect individuals differently. In the literature, HIV stigma (eg, discrimination experienced because of an HIV diagnosis) and medical mistrust (ie, distrust of providers or a medical system) often co-occur—a combination that directly affects HIV health outcomes among minorities [2]. In a recent study, medication mistrust was found to be directly related to HIV care adherence among African Americans [10]. HIV stigma is also known to be related to depression [2]. In examining strengths or coping mechanisms, resilience, which is defined as adaptation in the face of adversity, mitigates the negative barriers to positive health outcomes for minority women living with HIV [11].

In a public clinic in Miami, serving a predominantly minority population, a significant correlation was demonstrated between HIV care barriers and HIV care adherence. Depression and low patient-physician relationship ratings correlated significantly with low adherence. Moreover, patients who endured multiple barriers were more likely to have detectable viral loads [12]. HIV stigma, medical mistrust, and depression can be used to measure barriers to health care access. The relationship among these previously identified barriers, combined with a person’s resilience, may inform interventions to improve HIV care adherence.

### Objective

The overall goal of this innovative intervention is to develop a patient-centered mHealth system tailored to individual patients that addresses their unique HIV barriers. The system will deliver different text messages and will be designed for a cohort of multicultural and multilingual women living with HIV, who were followed up at a large, public academic medical center in Metropolitan Miami.

### Study Comparators

The control arm for this study are enrolled participants who will receive the hospital’s standard of care, as it relates to the reminders for clinical appointments. The hospital system mails reminder letters 7 to 10 days before the appointment. Patients also receive automated reminder telephone calls, approximately 2 working days before the appointment.

### Theoretical Foundation

Conceptually, the design of the intervention is consistent with the Health Belief Model (HBM) [13,14]. The HBM considers individual-level characteristics, strengths, and barriers to influence health behavior change. The mHealth system includes health reminders and psychoeducational (behavioral) messaging to reduce nonadherence, internalized stigma (one’s own negative perceptions about HIV), and medical mistrust while strengthening resilience. Behavioral messaging is adapted from the Dale and Safren’s Striving Towards Empowerment and Medication Adherence (STEP-AD) intervention, which aims to reduce nonadherence and the experiences of stigma and to improve resilience for women living with HIV [15]. The conceptual framework of the protocol is depicted in Figure 1.

**Figure 1 figure1:**
[figure not shown]
Protocol conceptual framework based on the Health Belief Model.

### Trial Design

This is a concurrent, two-phase, mixed method, pilot randomized controlled trial. Both the qualitative and quantitative components collect data from the target population women living with HIV. The trial begins with the qualitative component.

#### Phase 1

The qualitative component comprises interviews in the form of participant focus groups and participant key informant sessions.

#### Phase 2

The quantitative component is a short-term longitudinal intervention, where participants will be randomized to 1 of 2 study arms (parallel group). The allocation ratio is set at 1:1. The control arm will receive the standard of care for reminders, and the experimental arm will receive the intervention, in addition to the standard of care for reminders (see Study Comparators section). Data will be collected at baseline (T0), 3 to 4 months postbaseline (time 1; T1), and 6 to 9 months postbaseline (time 2; T2) after the launch of the intervention (exploratory trial).

## Methods

### Study Setting and Population

The study site is a women’s HIV clinic, located within an academic medical center in Metropolitan Miami, United States. Participants will be enrolled from various services of the clinic, including prenatal care, primary care, and gynecological specialty care.

### Eligibility Criteria

The following are the eligibility criteria for the study: (1) women aged ≥18 years; (2) confirmed HIV diagnosis (per the clinic’s standard); (3) active patient (ie, not withdrawn, transferred, or dismissed); (4) 2 or more previously scheduled visits 12 months before the study enrollment; and (5) nonadherence, based on 1 or more of the following criteria: missed 1 or more visits, having a viral load >20 copies/mL, or not taking HIV antiretroviral medications as prescribed.

Participants will have to confirm at the time of enrollment that they possess a working mobile phone number (to receive text messages). We will exclude women with serious psychiatric diagnoses, who are cognitively impaired or are not able to consent for themselves.

### Study Consent Process

Participants will give consent in person with the institutional review board (IRB)–approved paper copies of forms and an ink signature. First, clinic providers and staff will inform the patients of the study, including the purpose of the study and participation criteria. Second, patients who express interest in participating will be referred to a research team member who will be on site to provide further information. Potential candidates for the study will be read the informed consent form and the Health Insurance Portability and Accountability Act (HIPAA) form in their preferred language (English, Spanish, or Haitian Creole). A trained and IRB-approved study team member will explain the different aspects of the study in simple words and answer the study candidates’ questions. Interested candidates will then be asked 3 to 4 questions to assess the understanding of the project, purpose, procedures involved, and the voluntary nature of participation. Those who cannot successfully answer the questions will have the study re-explained by the research staff, with an opportunity for clarification on the areas that they did not understand. Only participants demonstrating an understanding of the study and voluntary agreement to participate will be invited to sign the forms. To accommodate low written literacy in the participants’ respective languages (Spanish or Haitian Creole), bilingual study team members will be on hand to ensure that the participants understand the questionnaires.

Before the beginning of each focus group, participants will be rebriefed on the purpose of the study and informed that the focus group will be recorded. Moreover, the participants will be informed of their right to remove themselves from the study or withdraw their responses at any time, without penalty. The respondents will also have the opportunity to ask questions before the session begins.

### Intervention Components

#### Qualitative Component

The qualitative component comprises 6 focus groups of 5 to 8 participants in each of the 3 different languages (English, Spanish, and Haitian Creole). Overall, 3 focus groups (focus groups before baseline; FG1), 1 per language, will occur before T0—the launch of the intervention. The second set of focus groups (focus groups at the end of the intervention; FG2) will occur at the end of the intervention (T2). The FG1s, conducted before T0, will inform the customization of the mHealth system; the FG2s, conducted after T2, will elicit the participants’ experiences with the intervention. The focus group participants will also complete the quantitative questions described in Table 1.

**Table 1 table1:** Summary of assessments and data collected for primary and secondary study outcomes.

Study outcomes			Study measures: description		Variable type and values		Data source (time point)	
**Primary outcomes**								
	**Rates of enrollment**							
				The proportion of participants enrolled out of the total number of participants approached. The proportion of participants who declined enrollment or failed the screening out of the total number of participants approached		Continuous; range 0-1		Study logs (T0^a^)

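### The primary enrollment outcome pools refusals with screen failures, so it cannot separate unwilling women from ineligible women

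*Protocol article*

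**What the plan says.** The abstract of the protocol article states: "The primary outcome is the feasibility and acceptability of the study". Table 1, under Rates of enrollment, turns the recruitment part of this into two measures, both taken from the study logs at baseline and both on a 0 to 1 scale. The first counts the women who joined: "The proportion of participants enrolled out of the total number of participants approached". The second counts those lost before joining, for either of two reasons, and uses the same denominator: "The proportion of participants who declined enrollment or failed the screening out of the total number of participants approached".

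No other section defines a refusal rate, a screen-failure rate or a rate of enrollment among eligible women.

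The Eligibility Criteria section gives several ways to fail screening. A woman must show "nonadherence, based on 1 or more of the following criteria: missed 1 or more visits, having a viral load >20 copies/mL", or not be taking her antiretrovirals as prescribed. She must be an active patient with at least two scheduled visits in the previous year. Women with serious psychiatric diagnoses are excluded, as are those "who are cognitively impaired or are not able to consent for themselves". On phones: "Participants will have to confirm at the time of enrollment that they possess a working mobile phone number".

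The Study Consent Process section adds a comprehension check: "Only participants demonstrating an understanding of the study and voluntary agreement to participate will be invited to sign the forms".

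**The concern.** A refusal and a screen failure carry different messages for the next trial. A refusal says something about the offer, the burden, the setting or the fear of disclosure. A screen failure says something about the criteria, about how candidates were found or, where a working phone is lacking, about the reach of a texting intervention. The first points to changing what is offered, the second to changing whom one approaches or what one requires.

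Table 1 puts both into one numerator. Ineligible women also stay in the denominator of the first measure, so enrolled over approached is a recruitment yield and not the willingness of eligible women. The study is presented as a feasibility pilot: that is the reason given under Power Analysis for having no power calculation, and the Conclusions section names a larger trial as the next step. An enrollment figure that cannot be traced to its cause gives the planners of that trial little to work with.

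**Working it through.** The article states no number approached and no enrollment target, so there is no figure of its own to reproduce. The check is an accounting one.

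**Notation.** A = approached, E = enrolled, D = declined, S = screen-failed, U = approached but in none of those groups. Then A = E + D + S + U.

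**The two measures in Table 1.** P1 = E/A and P2 = (D + S)/A, so P1 + P2 = 1 − U/A.

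- With U = 0, P2 = 1 − P1, and the second measure holds no information beyond the first.
- With A = 100, U = 5 gives a sum of 0.95 and U = 10 gives 0.90.
- In every case only D + S enters P2, so the split between D and S cannot be recovered.

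**What the pair leaves open.** Take U = 0 and treat every decliner as eligible. Uptake among eligible women is then E/(E + D). For fixed P1 and P2 it can lie anywhere from E/A (all non-enrolled women declined) to 1 (all failed screening).

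**Inputs for the example.** E = 54 is the enrollment count given in the Discussion as of April 2020, an interim count used only for scale. A = 100 is an assumption, so D + S = 46.

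| Declined | Screen-failed | P1 | P2 | Uptake among eligible |
|---|---|---|---|---|
| 46 | 0 | 0.54 | 0.46 | 54/100 = 0.54 |
| 23 | 23 | 0.54 | 0.46 | 54/77 = 0.70 |
| 0 | 46 | 0.54 | 0.46 | 54/54 = 1.00 |

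**Sensitivity to the assumed number approached (E = 54).** The upper end is always 1.00. The lower end is 54/A:

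| A | P1 | P2 | Range of uptake |
|---|---|---|---|
| 60 | 0.90 | 0.10 | 0.90 to 1.00 |
| 80 | 0.675 | 0.325 | 0.675 to 1.00 |
| 100 | 0.54 | 0.46 | 0.54 to 1.00 |
| 150 | 0.36 | 0.64 | 0.36 to 1.00 |
| 200 | 0.27 | 0.73 | 0.27 to 1.00 |

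**If screen failures are few.** With A = 100 and S = 5, uptake is 54/95 = 0.57. With S = 10 it is 54/90 = 0.60. Against P1 = 0.54, the gap is then about 3 to 6 percentage points.

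**The case against.** Several points on the other side carry weight.

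- **Screening before approach.** Recruitment Strategy says that missed appointments, medication adherence, viral load and language are drawn from the clinic database for potential participants with a confirmed appointment. Most of the nonadherence criterion can therefore be checked in advance. Clinic staff also mention the participation criteria before referring interested women. Screen failures are probably few, and the pooled measure would then lie close to the refusal rate. This stands, and it limits the likely size of the problem. It does not remove it. The article does not say that only pre-identified women are approached, and the extracted items it lists do not include phone access or capacity to consent.
- **Exact complementarity.** A reader might infer that the two proportions must add to 1. The article does not establish this. A woman who does not pass the comprehension check might be logged as a screen failure, since inability to consent is an exclusion, or in no category. Reporting a rate beside its complement would in any case be harmless redundancy. The point about the pooled numerator does not depend on exactness.
- **Opposite decisions.** A reader might also infer that the two causes would lead to contrary go or no-go decisions. No progression rule or threshold is stated, so the documents do not support that.
- **Acceptability.** Refusal need not mean that texting is unacceptable. Women may decline for other reasons, and Table 1 measures acceptability separately, by messages opened.
- **Detail left to a fuller document.** An article may leave reasons for non-enrollment to the full protocol, and the study logs may already hold them. But Table 1 does not merely omit a breakdown. It states a pooled definition for a primary outcome. If the reasons are already logged, the correction costs even less.

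**Conclusion.** The point holds as a weakness in the definition of a primary outcome. Declines and screen failures share one numerator, nothing else in the article separates them, and ineligible women remain in the denominator of the enrollment rate. This follows from the wording of Table 1 alone. The further statement that the second measure equals 1 minus the first needs every approached woman to be logged as enrolled, declined or screen-failed.

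The span from 54% to 100% uptake assumes 100 approached and is an outer bound, not an expected error. If prior extraction keeps screen failures to 5 to 10 per 100, the understatement of uptake is a few percentage points, but the pooled figure could not show that this was so. A reader should not conclude that a screen failure reflects only a broad approach list: lack of a working phone is itself a barrier to a texting intervention. Nor does the article show that data capture is deficient. The trial remains valid. Its enrollment figure, as defined, is a weak guide for the larger study, and the definition should be corrected.

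**What to change.** Change the enrollment row of Table 1 as follows.

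1. Keep enrolled over approached, labelled as recruitment yield.
2. Replace the pooled measure with separate counts and proportions for declines and for screen failures. Show failures for lack of a working phone on their own line.
3. Add enrolled over women known to be eligible. Show women who declined before their eligibility was known as their own category, and give uptake twice: with them left out of the denominator and with them included.
4. State how a woman who does not pass the comprehension check is counted, so that the categories account for everyone approached.

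The cost is one reason code per approached woman in the study log, if it is not already there, and an edit to one table row. No extra participants, visits or assessments are needed. The remaining limitation is that uptake will be a range wherever women decline before eligibility is known. The two versions in step 3 show how wide that range is.

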	**Acceptability of the mobile health app**							
				The proportion of messages opened out of the number of messages received		Continuous; range 0-1		Data usage logs (T0, T1^b^, and T2^c^)
**Secondary outcomes**								
	**Clinical outcomes**							
		Adherence to medication		Wilson 3-item self-report measure for medication adherence (self-administered) [16]		Continuous (score); range 1-100		Participant (T0, T1, and T2)
		Clinic attendance (change)		Number of missed visits 1 year before assessment (T0), between T0 and T1, and between T1 and T2		Continuous (number)		Electronic medical record
		Viral suppression		Viral load		Categorical; ≥20 copies/mL or <20 copies/mL		Electronic medical record or measured through a blood test (T0, T1, and T2)

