### Intervention Fidelity

#### Laboratory Data

If participants miss their scheduled clinical appointment, they will be asked to come to the clinic’s research wing, where a blood sample will be drawn by a clinical research staff member to obtain the viral load. Quantitative data will be collected as well. This procedure will ensure adherence to study data points T1 and T2.

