### Study Outcomes

The primary and secondary outcomes are summarized in Table 1. Data will be collected either from the electronic medical record (EMR), the HIV database, or directly from the participants’ responses to questionnaires. For analysis, all outcomes (Table 1) will be reported as a change from baseline. As this is a pilot study, our intention is to determine the most sensitive measures. We will explore the data to determine the most suitable categorizations for a future study; therefore, the total scores will be reduced to categories once all data have been compiled. To report on the participant characteristics, sociodemographic data, including age, race/ethnicity, HIV or AIDS status, socioeconomic status, pregnancy status, substance use, and mental health history (past year), will be collected at T0.

Clinical outcomes (at T0, T1, and T2) that will be examined include a comparative history of self-reported medication adherence, visit attendance, and viral suppression reported as the biological marker of HIV viral load (copies/mL). Psychological and behavioral data include depressive symptoms, internalized stigma, resilience, and medical mistrust (Table 1).

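### Clinic attendance is only a count of missed visits, with no scheduled or kept visits, so leaving care with nothing booked is invisible and better retention can look like worse attendance

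*Protocol article*

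**What the plan says.** Table 1 lists clinic attendance among the three clinical secondary outcomes. It is a continuous number from the electronic medical record, defined as "Number of missed visits 1 year before assessment (T0), between T0 and T1, and between T1 and T2". The abstract likewise has "clinic attendance and viral suppression extracted from the participants’ medical records". Under Study Outcomes, "For analysis, all outcomes (Table 1) will be reported as a change from baseline".

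Bookings are guaranteed only before entry. Eligibility Criteria asks for "2 or more previously scheduled visits 12 months before the study enrollment" and for current-patient status at the clinic. No section requires or counts scheduled visits after T0, counts visits kept, or says how a window with no booking is scored.

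Three other places bear on such a woman:

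- The abstract's Methods places T1 and T2 at two later clinic visits.
- Laboratory Data offers a back-up: "If participants miss their scheduled clinical appointment, they will be asked to come to the clinic’s research wing".
- Data Preparation and Statistical Analysis: Missing Data set missing values aside and limit each test to complete records.

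**The concern.** A missed visit needs a booking. The count therefore mixes two things: how many visits a woman has booked, and how many of those she fails to keep. Being in care raises the first, so a woman who stays in care is exposed to missing visits and a woman who has left with nothing booked is not. A woman who misses one visit and never rebooks scores 1, the same as a woman who books four and keeps three.

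The article gives reasons to expect loss from care. Rationale notes that "Postnatal women, who may be adequately engaged in HIV care, for example, fall out of care after the birth of their child", and under Study Setting and Population "Participants will be enrolled from various services of the clinic, including prenatal care, primary care, and gynecological specialty care". Strengths and Limitations warns that retention may suffer.

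At stake is the attendance result itself. An intervention that keeps women in care could appear to have no effect on attendance, or a harmful one. Study Outcomes and Power Analysis say the pilot is to find the most sensitive measures and estimate effect sizes, so the error would be carried into planning the later trial.

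**Working it through.** **Inputs.** The outcome definition is from Table 1. Arm size is from Assignment to Study Arms: about 10 per language per arm, so 3 × 10 = 30 per arm. The article states no visit rate, miss rate, retention rate or attendance effect, so there is no figure to reproduce. All values below for these are assumptions:

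- r = share of women still booking visits after T0
- V = visits booked per retained woman from T0 to T2
- m = probability that a booked visit is missed

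Women who leave are taken to have nothing booked from T0 onward.

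**Reading 1: a window with no booking counts as zero missed visits.** Per randomized woman:

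- mean missed = r × V × m
- mean kept = r × V × (1 − m)

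With the same V and m in both arms, the ratio of mean missed visits is r(intervention) / r(control), whatever V and m are. Randomization equalizes baseline counts on average, so the expected difference between arms is the same for change from baseline.

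| Assumptions (control v intervention) | Missed | Ratio | Kept |
|---|---|---|---|
| V = 4, m = 0.30, r = 0.80 v 0.95 | 0.96 v 1.14 | 0.95/0.80 = 1.19 | 2.24 v 2.66 |
| V = 3, m = 0.30, r = 0.70 v 0.90 | 0.63 v 0.81 | 0.90/0.70 = 1.29 | 1.47 v 1.89 |

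**Break-even.** For the raw count to show no difference, the intervention arm's miss probability must equal m × r(control) / r(intervention). In the first row this is 0.96 / (0.95 × 4) = 0.253, down from 0.30. The relative reduction needed is 1 − r(control) / r(intervention):

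- 80% v 90%: 11%
- 80% v 95%: 16%
- 70% v 90%: 22%
- 60% v 90%: 33%

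**With a true benefit on missed visits.** Take V = 3, r = 0.70 v 0.90 and m = 0.35 v 0.30. Missed visits are 0.70 × 3 × 0.35 = 0.735 and 0.90 × 3 × 0.30 = 0.81, so the intervention looks worse. Missed out of scheduled is 0.35 v 0.30, and kept visits are 0.70 × 3 × 0.65 = 1.365 v 0.90 × 3 × 0.70 = 1.89. Both point the right way.

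**At the planned size.** In 20,000 simulated trials with 30 per arm, V = 3 and retention 70% v 90%, the intervention arm had the higher mean missed count in about 78% when m was 0.30 in both arms. When m truly fell from 0.35 to 0.30, it did so in about 61%.

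**Absolute size if visits are sparse.** Two visits a year, the entry minimum, gives V = 1 to 1.5 over 6 to 9 months. With m = 0.30 and retention 80% v 95%, the gap is 0.15 × V × 0.30 = 0.045 to 0.068 missed visits per woman, against 0.18 at V = 4. The 19% ratio is unchanged.

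**Reading 2: she has no T1 or T2 date and is excluded.** Under the first row's assumptions, women left in the analysis miss 4 × 0.30 = 1.20 visits in both arms. The sign does not reverse, but the difference in retention (80% v 95%) disappears from the attendance result.

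**The case against.** The strongest reply is that the article nowhere says a woman with nothing booked scores zero. T1 and T2 are clinic visits, so her window may have no end date and the complete-record rule may drop her. This stands. A reader might infer that disengagement is definitely scored as the best result; the text supports that only as one of two readings. Dropping her is no remedy, because her loss from care then leaves the comparison altogether. The research-wing call-back does not settle it either, since it is triggered by missing a scheduled appointment.

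A reader might also infer that the article itself predicts this pattern, because it enrols prenatal patients and describes postnatal women leaving care. That is background. It does not say they leave with nothing booked, and a woman who stops coming while an appointment stands is counted as missing it. The worked scenarios, with every leaver gone at T0 and nothing booked, are the extreme case.

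The rates have no source in the article, and reversal needs a retention difference that is large relative to any effect on missing booked visits. That also stands.

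Finally, missed visits are a behaviour that reminders target and an entry criterion, and the outcome is secondary in a pilot with no power claim. This limits the importance of the point but does not remove it. Nor is this a detail left to an analysis plan: Table 1 fixes the outcome as a count of missed visits. Only the scoring of a window with no booking could be settled elsewhere.

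**Conclusion.** The point holds in this form: the attendance outcome counts missed visits without scheduled or kept visits, so it cannot register loss from care with nothing booked, whether such a woman is scored zero or excluded. If she is scored zero and miss probability is equal between arms, the better-retaining arm shows more missed visits in proportion to retention: 19% more at 80% v 95%, 29% more at 70% v 90%. These sizes rest on assumed rates and on leavers having no outstanding booking.

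The stronger reading, that the sign of the effect will reverse, is not supported. It depends on retention rates and a scoring rule that the article does not give. Equal windows or a monthly rate would not cure the fault, since nothing booked still gives nothing missed. The primary feasibility outcomes are unaffected. What is affected is the attendance effect size and the judgement of which measures are sensitive, both of which the pilot is meant to pass on to a larger trial.

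**What to change.** Change the clinic attendance row of Table 1:

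1. From the same appointment data, record visits scheduled and visits kept as well as missed. Recruitment Strategy and Instrumentation already provide for extracting appointments and visit history.
2. Make the attendance outcome kept clinic visits for every randomized woman over one fixed calendar period from T0 to the end of follow-up, for example 9 months, the outer limit of T2. Use the count, or at least one kept visit over the whole period. Women with nothing booked are then included. Do not require a kept visit in each short window, because a woman with no visit due in the 3 to 4 months before T1 would be labelled non-attending.
3. Report missed out of scheduled visits as a supporting measure among women with a booking. It cannot stand alone, because it is undefined for the women who left.
4. Keep the raw missed-visit count as descriptive, and state how a period with no booking is handled.
5. State that a research-wing call-back is not a kept clinic visit.

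The cost is a wording change and one more field from the record. A yes/no measure is coarser than a count. Kept visits also vary with how often a woman is due to be seen, which randomization balances between arms on average, though with about 30 per arm some chance imbalance is possible.
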